#### Mental health

The Hospital Anxiety and Depression Scale comprises 14 items, including seven items on anxiety and seven items on depression in the past week in participants with physical illnesses and physical complaints. More precisely, it measures the participants’ self-assessed level of anxious and depressive symptoms in relation to the past week.^75^ Participants’ current perception of stress is assessed using the Perceived Stress Scale-10 Item Version.^76^ This questionnaire measures the participants’ current subjective perception of stress using 10 items in the four subscales of worry, tension, pleasure and demands.^77^

#### Sleep quality

The Pittsburgh Sleep Quality Index uses 24 items, 17 for self-assessment and seven for external assessment, to measure the quality of sleep over the past 4 weeks. It is used in clinical settings to monitor patients with sleep disorders and to screen for sleep disorders in epidemiological studies.^78^ In this study, only the 17 self-assessment items are collected.

#### Hand grip strength

HGS is measured in kilograms using a digital hand dynamometer (CAMRY, model: SCACAM-EH101) as an objective parameter of muscular fatigue. The participants complete two separate rounds of pulling 10 times for 3 s with maximum force, the second round in a distance of 1 hour to the first, spaced by filling out questionnaires as a muscular recovery break of 60 min. The participants are supervised by a study nurse or study physician and not allowed to see their HGS. Within the 3 s of pulling time, the CAMRY dynamometer measures the maximum pulling strength. The measurement with the highest value out of the 10 repetitions is recorded as maximum strength of the round.

### Laboratory parameters

Leucocytes, lymphocytes, D-dimers, C reactive protein, interleukin-6 and LDH are determined from blood samples as parameters for the inflammatory reaction, pro-inflammatory cytokine activity and cell damage.^26^

### Real-world physical activity assessment

The EC-certified sensor (Axivity AX6, Axivity, Newcastle, UK) used in this study includes an accelerometer and a gyroscope. It records the duration of activity and is able to objectively quantify different activity domains, which are related to the physical fatigue and PEM frequency of patients. The sensor is placed centrally on the lower back, close to L5, and is attached with a skin-friendly and waterproof plaster. The sensor is worn continuously for 7 days over 24 hours and can be worn during all daily activities, including showering. A software platform is used to process the raw sensor data (McRoberts, The Hague, The Netherlands).

The following activity parameters are derived for each day of the study using validated algorithms:

Cumulative activity time (total and specific activities, eg, walking, shuffling, cycling, standing and static).Number of transitions (eg, sit-to-stand transfers).Number of periods (eg, number of walking bouts total and with specific durations, eg, >10 s).Number of steps (average, minimum, maximum, range).Walking speed (average, minimum, maximum, range).Walking distance (total, maximum within a bout).Duration of activity in specific metabolic equivalent (MET) ranges (eg, total duration of periods below three METs).

The following non-activity parameters are also derived for each day of the study:

Cumulative non-activity time (total and specific non-activities: lying and sitting).Cumulative lying during daytime and nighttime.Movement during lying time (eg, duration, number of periods).

### Heart rate variability

The 24-hour measurement of HRV is used to determine the functionality of the participant’s autonomic nervous system. A 3-channel ECG recorder (SRA/Multi-ECG recorder, SR-Medizinelektronik, Stuttgart, Germany) is used. Several HRV time-domain and HRV frequency-domain measures will be evaluated and analysed for the total day and night (sleeping time) period as well as for 5 min intervals within these two periods (table 1).^79^

**Table 1 T1:** HRV measures

HRV time-domain measures		
**Parameter**	**Unit**	**Description**
SDNN	ms	SD of NN intervals
RMSSD	ms	Root mean square of successive RR interval differences
pNN50	%	Percentage of successive RR intervals that differ by >50 ms
SDANN	ms	SD of the average NN intervals for each 5 min segment of a 24-hour HRV recording
SDNNI	ms	Mean of the SD of all the NN intervals for each 5 min segment of a 24-hour HRV recording
**HRV frequency-domain measures**		
**Parameter**	**Unit**	**Description**
VLF power	ms^2^	Absolute power of the very-low-frequency band (0.0033–0.04 Hz)
LF power	ms^2^	Absolute power of the low-frequency band (0.04–0.15 Hz)
LF power	%	Relative power of the low-frequency band (0.04–0.15 Hz)
HF power	ms^2^	Absolute power of the high-frequency band (0.15–0.4 Hz)
HF power	%	Relative power of the high-frequency band (0.15–0.4 Hz)
LF/HF	%	Ratio of LF-to-HF power

HRV, heart rate variability.

### Health economics

The societal cost-effectiveness and cost-utility analyses will be conducted to compare the costs as well as the effect and utility of the yoga and health education group. Accordingly, all relevant costs will be included in the economic evaluation. The cost-effectiveness analysis will use the CFQ score as the outcome measure, while the cost-utility analysis will use quality-adjusted life years (QALYs).^80^ The incremental cost-effectiveness ratio is calculated based on the incremental costs and incremental CFQ scores. Similarly, the incremental cost-utility ratio (ICUR) is calculated based on the incremental costs and incremental QALYs (figure 2).^81^

**Figure 2 F2:**

Incremental cost-utility ratio (ICUR).

### Measuring costs

The end of the intervention, that is, 12 weeks after randomisation, and 24 weeks after randomisation are the time points for cost collection. In order to capture all relevant costs for an economic analysis, the social perspective is chosen. Thus, intervention costs, direct medical and non-medical costs as well as productivity losses are considered. All costs are expressed in euros (€).

Direct medical and non-medical costs are collected using a participant-completed questionnaire. The questionnaire is a modified version of the Cost for Patient Questionnaire,^82^ designed to collect all information on healthcare costs. Costs are assessed according to their standard price or according to the reimbursement system in Germany. The direct costs of the interventions are collected during the intervention, recorded in the study documents and valued at their actual cost. Indirect costs are expressed in terms of productivity losses and are recorded in the participant questionnaire. Productivity losses for employed participants are estimated by multiplying the productivity hours lost by the average national employment cost. Productivity losses are included in the sensitivity analysis.

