### Health economic analysis

As the analysis does not cover a period of >1 year, it is not necessary to discount the costs and QALYs incurred. Descriptive analyses will be conducted to determine the costs incurred in the yoga and health education group. Regression models will be used to identify possible predictors of cost or outcome differences. Due to the assumptions made and the estimated costs, there is a degree of uncertainty in the economic analyses. Thus, sensitivity analyses are performed to determine the robustness of the estimates to various assumptions.^93^ In addition, means and 95% CIs are estimated by bootstrapping using the observed distributions of the cost data in the analysed study.^94 95^ To summarise the uncertainty in the cost-effectiveness and cost-utility estimates, the cost-effectiveness acceptability curve and the cost-utility acceptability curve are calculated.^96^ The curves illustrate the probability that the cost-effectiveness or cost-utility ratio of the yoga intervention falls below a specified willingness-to-pay threshold.

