This study is characterised by several methodological strengths. By comparing yoga with an active control condition—health education—it accounts for non-specific effects such as attention, social support and group interaction, thereby enabling a more accurate assessment of yoga’s specific therapeutic impact. The study also adopts a comprehensive assessment strategy that includes both subjective outcomes, such as self-reported fatigue and quality of life, and objective measures, such as HGS, HRV and laboratory parameters. Additionally, health economic analyses and qualitative interviews provide a multidimensional evaluation of intervention outcomes. Importantly, the economic evaluation takes a societal perspective, incorporating both direct and indirect costs, thereby offering valuable insights for health policy and resource allocation.

Nonetheless, several limitations should be acknowledged. As with many clinical trials, the generalisability of the findings may be limited, as the sample may not fully represent the broader post-COVID-19 population, particularly individuals with severe comorbidities or differing sociodemographic characteristics. While self-reported measures such as fatigue and quality of life are essential for capturing patient perspectives, they are subject to reporting bias. This limitation is partially mitigated by the inclusion of objective outcome measures. The follow-up period of 24 weeks allows for the evaluation of medium-term effects, but long-term outcomes remain to be determined. Additionally, participant blinding is not feasible in behavioural interventions such as yoga, which may introduce expectancy effects and influence self-reported outcomes.

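### Productivity losses are assigned to the sensitivity analysis of an evaluation described as societal, and the acceptability curves are described by a ratio rule that, taken literally, misclassifies results

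*Protocol article*

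**What the plan says.** **Costs.** The Health economics section of the protocol article announces societal cost-effectiveness and cost-utility analyses and adds: "Accordingly, all relevant costs will be included in the economic evaluation". Measuring costs repeats the commitment: "In order to capture all relevant costs for an economic analysis, the social perspective is chosen". It continues: "Thus, intervention costs, direct medical and non-medical costs as well as productivity losses are considered". The same section equates indirect costs with productivity losses, values them as hours lost times average national employment cost, and closes with "Productivity losses are included in the sensitivity analysis". No other cost component is assigned to a particular analysis. The Discussion states as a strength that "the economic evaluation takes a societal perspective, incorporating both direct and indirect costs".

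**Ratios and curves.** Under Health economics, the incremental cost-effectiveness "ratio is calculated based on the incremental costs and incremental CFQ scores". A second ratio uses QALYs. Under Outcome measures, the CFQ (0 to 33) measures fatigue severity, so a benefit of yoga is a negative difference when health education is subtracted from yoga. Health economic analysis describes the acceptability curves as follows: "The curves illustrate the probability that the cost-effectiveness or cost-utility ratio of the yoga intervention falls below a specified willingness-to-pay threshold".

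**The concern.** There are two separate problems.

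**Cost set.** A societal evaluation whose base case omits productivity losses is in substance a direct-cost evaluation. The Background section says that post-COVID-19 fatigue affects work capacity and carries high socioeconomic costs, so this component could be large enough to change the sign or size of the incremental cost. If the base case is not fixed, either result could be presented as the main one after the data are seen.

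**Decision rule.** A cost-effect ratio does not show which quadrant of the cost-effectiveness plane it came from. A negative ratio can mean better and cheaper, or worse and dearer. A positive ratio can mean better and dearer, or worse and cheaper. Counting the ratios below a threshold treats the members of each pair alike. The CFQ adds a further trap, because improvement is a fall in the score.

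Cost-effectiveness is a stated aim, and the article says the economic analysis could justify wider implementation.

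**Working it through.** **Step 1. The cost set: passages side by side.** The article gives no cost data, so there is no figure to reproduce.

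- Health economics: all relevant costs are included.
- Measuring costs: productivity losses are among the costs considered and are the definition of indirect costs.
- Discussion: direct and indirect costs are both incorporated.
- Last sentence of Measuring costs: productivity losses, alone among the components, are placed in the sensitivity analysis.

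If they are outside the base case, the last statement conflicts with the other three. If they are inside it, the last sentence does not say so. Moving them in or out shifts the cost-utility ratio by (difference in mean productivity cost) / (difference in mean QALYs). That shift cannot be sized from the documents.

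**Step 2. The ratio rule in general.** Let E be the health gain of yoga over health education, C the cost difference, λ the threshold, and NB = λE − C the incremental net benefit. Yoga is cost-effective when NB > 0.

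- If E > 0: C/E < λ is equivalent to C < λE, that is NB > 0. The rule is right.
- If E < 0: C/E < λ is equivalent to C > λE, that is NB < 0. The rule is exactly reversed.

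So the share of ratios below λ equals P(E > 0 and NB > 0) + P(E < 0 and NB < 0). Worse-and-dearer replicates always pass. Worse-and-cheaper replicates are classified backwards. This is algebra and needs no assumed figure.

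**Step 3. CFQ examples.** The 3.3 points come from the sample size section; λ = 100 euros per point and the costs are assumed. The unreversed ratio is C divided by the CFQ difference (yoga minus health education). The reduction ratio uses health education minus yoga.

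| Yoga | C (euros) | Unreversed ratio | Reduction ratio | NB |
|---|---|---|---|---|
| 3.3 better | +600 | −182, passes | 182, fails | 330 − 600 = −270 |
| 3.3 better | −600 | 182, fails | −182, passes | 330 + 600 = +930 |
| 3.3 worse | +200 | 61, passes | −61, passes | −330 − 200 = −530 |
| 3.3 worse | −600 | −182, passes | 182, fails | −330 + 600 = +270 |
| 3.3 worse | −200 | −61, passes | 61, passes | −330 + 200 = −130 |

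Unreversed, the rule is wrong in rows 1, 2, 3 and 5. Reversed, rows 1 and 2 are right and all three worse rows are wrong.

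**Step 4. QALY examples** (assumed λ = 20,000 euros; yoga 0.02 QALY worse).

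- +200 euros: ratio −10,000, passes; NB = −400 − 200 = −600.
- −600 euros: ratio 30,000, fails; NB = −400 + 600 = +200.
- −200 euros: ratio 10,000, passes; NB = −400 + 200 = −200.

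**Step 5. Size when there is no true difference.** For independent normal C and E centred at zero, the literal rule gives 1/2 + arctan(k)/π, with k = λ × SE(E) / SE(C). The correct value is 1/2. Only k matters, so its range covers all assumptions about spread:

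| k | 0.1 | 0.3 | 0.75 | 1 | 1.5 | 3 |
|---|---|---|---|---|---|---|
| Literal rule | 53% | 59% | 70% | 75% | 81% | 90% |

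With assumed SE(C) = 800 euros and SE(E) = 0.012 QALY, thresholds of 20,000, 50,000 and 100,000 euros give k = 240/800 = 0.3, 600/800 = 0.75 and 1,200/800 = 1.5. As λ rises, the curve tends to 100% whatever the treatment. With yoga 300 euros dearer and 0.01 QALY worse, λ = 20,000 gives 69% under the literal rule (simulated). Correctly, mean NB = −200 − 300 = −500 and its SD = √(240² + 800²) = 835, so P(NB > 0) = Φ(−0.60) = 27%.

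**Step 6. Size for the CFQ (simulation, 400,000 draws).** SE(E) = 4.4 × √(2/50) = 0.88, from the article's SD and 50 per arm. SE(C) = 1,500 × √(2/50) = 300 euros, with the cost SD of 1,500 assumed.

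| Yoga | C (euros) | λ | Unreversed | Reduction | P(NB > 0) |
|---|---|---|---|---|---|
| 3.3 better | +300 | 50 | 0.94 | 0.33 | 0.33 |
| 3.3 better | +300 | 200 | 1.00 | 0.85 | 0.85 |
| 3.3 better | −300 | 50 | 0.33 | 0.94 | 0.94 |
| No effect | +300 | 50 | 0.53 | 0.53 | 0.16 |
| 3.3 worse | +300 | 50 | 0.33 | 0.94 | 0.06 |

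Reversing the sign cures the yoga-better cases, but not the null or adverse ones.

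**The case against.** **Productivity losses.** The closing sentence does not say that they appear nowhere else. Health economic analysis says sensitivity analyses test robustness to assumptions, and productivity losses are an estimate that rests on an assumed unit cost. They could stay in the base case and also be varied. A reader might infer that the plan definitely excludes them; the text does not establish that. What stands is that the natural reading conflicts with three other statements and that no sentence fixes the base case.

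**CFQ sign.** The article fixes neither the order of subtraction nor the sign, and orienting a symptom scale is detail that an article may leave to the full protocol or analysis plan. A reader might infer that the unreversed score will be used; that is not shown. The largest discrepancies (0.94 against 0.33) depend on it.

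**Curves.** Describing an acceptability curve as the chance that the ratio is below the threshold is common shorthand. The sentence says what the curves show, bootstrapping is mentioned for means and intervals of costs, and the computation may well use net benefit. A reader might infer that ratios will be counted; the article does not prescribe that algorithm. What stands is that this is the only definition given and that it is wrong if followed.

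**Size.** No costs, spreads or thresholds are stated. Equal session time in both arms makes similar intervention costs plausible, but says little about healthcare use or lost work.

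**Conclusion.** The point holds as two matters to correct in the secondary economic evaluation.

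First, the placement of productivity losses does not fit the declared societal perspective on its most natural reading, and the base-case cost set is left open. It would go too far to say that the plan excludes these losses from the base case.

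Second, the described ratio rule, if applied literally, reverses the decision wherever yoga is less effective, for CFQ and QALYs alike. It also fails in the yoga-better quadrants if CFQ differences are not reversed. It would go too far to say that the analysis will misclassify results, since net benefit may be what is intended.

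The direction of the error is algebraic, but its size is not known. Under no true difference it runs from a few percentage points to about 40 as k goes from 0.1 to 3, assuming independent normal cost and effect differences. The primary analysis of fatigue and the data collection are unaffected.

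**What to change.** - **Cost set.** Reconcile Health economics, Measuring costs and the Discussion by stating that productivity losses are in the base case, with the analysis without them as the sensitivity analysis.
- **CFQ effect.** Define it as points of reduction, health education minus yoga, so that a positive value favours yoga.
- **Curves.** Define each as the share of bootstrap replicates with λ × effect − cost above zero. Resample each participant's cost and effect together, and show the replicates on the four-quadrant plane.

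The cost is a change of analysis wording; the data needed are already collected. The price is a noisier base case, because productivity costs vary widely between participants.

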### Measuring utility

Utility of the intervention is measured by calculating QALYs using the EQ-5D-5L questionnaire at baseline, after 12 weeks and after 24 weeks.

The EQ-5D-5L is a preference-based generic instrument for measuring health-related quality of life.^83^ It consists of a self-assessment section and a EuroQol visual analogue scale (VAS). The self-assessment comprises a five-level classification system for five dimensions of quality of life. On the VAS, participants rate their health-related quality of life on a scale from 0 mm to 100 mm. The main advantage of the EQ-5D-5L over the SF-12 is that it provides a preference-based quality of life index score across all dimensions, which is necessary for calculating QALYs and conducting a cost-utility analysis. For this reason, it is used in addition to the SF-12.^84 85^

QALYs are calculated by recording utilities at each follow-up point and estimating the area under the curve based on social preference weights provided by the EuroQol group. To avoid bias, we will adjust for differences in baseline EQ-5D-5L scores.

### Potential mediating variables

#### Body awareness

BAQ assesses participants’ subjective body awareness in four subdimensions: note responses or changes in body processes, predict bodily reaction, sleep-wake cycle and onset of illness. The validated single-factor German version consists of 17 questions on a 7-point Likert scale from 1 (not at all true about me) to 7 (very true about me). The values of the individual items are added together to form a total score.^86 87^

#### Self-efficacy

The Arthritis Self-Efficacy Scale (ASES) was originally developed as part of the Stanford Arthritis Self-Management Study to assess self-efficacy in patients with arthritis and has since been used to assess this construct in many clinical pictures. A short version (ASES-8/ASES-D) has been validated. This version measures the perceived ability to deal with symptoms such as pain or fatigue on a scale ranging from 1 to 10.^88^

### Potential moderating variables and covariates

#### Personality traits

The Big Five Inventory-10 is a questionnaire for the efficient assessment of the five dimensions of personality according to the five-factor model (Big Five model). It consists of 10 items. Two items each (one positive and one negative) are used for each of the five main dimensions of personality (extraversion, agreeableness, conscientiousness, neuroticism and openness to experience). The answers are given on a 5-point rating scale ranging from 1 (strongly disagree) to 5 (strongly agree). The values on the two items are aggregated into one scale value.^89^

#### Treatment credibility and expectations

The Credibility Expectancy Questionnaire is used to measure treatment credibility and expectations at the beginning of the study via six items using 9-point Likert scale.^90^

#### Safety management protocol 

AEs (containing all undesirable symptoms, illnesses, disorders or accidents), including PEM, are documented weekly by participants and reviewed by the study team every 2 weeks. Serious adverse events (SAEs) including events that are immediately life-threatening and/or result in serious health problems (in particular, require unplanned hospitalisation or prolongation of hospitalisation or result in serious disability or incapacity) must be reported immediately by direct telephone contact with the study site. PEM is systematically assessed for baseline and follow-ups using the validated PEM subscale of the DSQ and complemented by weekly symptom diaries. Predefined safety thresholds for modifying or discontinuing the intervention include (i) marked exacerbation of fatigue or other core symptoms persisting for >48 hours, (ii) deterioration in daily functioning that interferes with activities of daily living or (iii) occurrence of an SAE. Instructors and study physicians are authorised to adapt or interrupt the intervention in such cases. If participants are absent from two sessions due to health-related reasons, the site physician will discuss with them whether continued participation is considered safe and appropriate. No fixed cut-off score (eg, point value on Bell Score) was applied for exclusion. Instead, participants’ functional capacity was evaluated verbally during the physician-led informed consent visit, where risks and potential burdens of study participation were explained. This structured monitoring and safety management protocol is designed to minimise risk while ensuring the inclusion of a representative post-COVID-19 patient population.

